### Study Procedures

All full-time therapists at both study sites who volunteer to participate will be consented. We project 4 therapists at each site (N=8) will participate. As in the authors’ previous work [79], clinic staff will discuss the research opportunity with the families of all the adolescents during routine intake procedures. If consent is given, clinic staff will send the family’s contact information to the study team through secure channels. The study team will contact interested caregivers by phone to complete (1) consent to phone screen, audio record sessions, complete outcome interviews and questionnaires, and grant access to clinic records and (2) an eligibility screener assessing IDs. IDs will be assessed using the Achenbach System of Empirically Based Assessment Child Behavior Checklist [122], a well-validated assessment method for screening for depression and anxiety problems in youth. IDs will also be assessed during the baseline research assessment using the Mini-International Neuropsychiatric Interview for Children and Adolescents [123,124], a structured diagnostic interview administered by lay interviewers; the interview yields Diagnostic and Statistical Manual of Mental Disorders, Fifth Edition, Text Revision categories and has been used in diverse adolescent samples [79,125]. Client data on protocol viability (limited to Fam-AID cases only) and clinical outcomes will then be collected on all study clients (regardless of amount of treatment participation) at baseline, 3-month, and 6-month follow-up using REDCap (Research Electronic Data Capture; Vanderbilt University) cloud software, a widely used and secure Health Insurance Portability and Accountability Act (HIPAA)–compliant, web-based data collection platform.

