### Study Measures

#### Fam-AID Fidelity Checklist

This study will use an adapted version of the Inventory of Therapy Techniques (ITT [95,96]), a postsession therapist-report fidelity tool that requires 1 or 2 minutes to complete. ITT items are designed to measure the extensiveness (ie, thoroughness and frequency) with which a given treatment technique was used on a 3-point Likert-type scale: 0 (not at all), 1 (a little bit or moderately), or 2 (quite a bit or extensively). ITT items are derived from treatment protocols and their associated observational fidelity tools, for example, for family therapy [51] and for CBT [67], after being vetted for relevance by community clinicians in multiple treatment settings [134]. ITT has shown strong construct [50,134] and predictive [79,135] validity in studies with adolescents receiving family therapy and CBT in usual care. The Fam-AID Fidelity Checklist mimics the ITT structure, containing multiple items in each of the 5 Fam-AID modules: culturally attuned family engagement, relational reframing of ID symptoms, functional analysis of ID symptoms, CBT treatment techniques for ID, and SUD+ID education and safety planning. The Fam-AID Fidelity Checklist–Observer Version is an identical measure with instructions for observer coding.

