*Aim 1 fidelity benchmarks* analyses (Fam-AID condition only) will examine both types of previously described fidelity metrics. Regarding coverage, descriptive statistics will capture frequencies related to (1) proportion of clients who received at least 1 intervention from each of the 5 modules and (2) interventions from which modules were most or least favored across clients. Chi-square analysis will be used to compare study conditions on the proportion of clients who received adequate coverage and conduct one-way analysis of variance to assess mean differences across modules in the Fam-AID condition to evaluate module preferences among therapists. Regarding dose, statistical equivalence testing [153] will be used to examine whether clinicians’ average scores for intervention extensiveness on both observer- and therapist-report versions of the Fam-AID Fidelity Checklist are equivalent to a designated benchmark, which will be set (granting appropriate latitude for a pilot trial) for each module as mean 2.5 (SD 0.50). A CI approach will be adopted in which an equivalence interval is defined as the benchmark +10% and –10%. Next, a CI is defined by the following formula: CI_90%_=M_R_–M_T_+/–z_α_(S_MR−MT_). In this equation MR represents the benchmark module mean, MT the average module score for study therapists, zα the critical one-tailed value from the z distribution for the chosen value of α, and SMR−MT the pooled SE. If the calculated CI falls within the equivalence interval, equivalence can be concluded. In addition, therapist variability in Fam-AID fidelity will be examined via statistical process control analyses (refer to the study by Hogue and Dauber [125]) in which individual therapist fidelity scores are plotted on a control chart to check for meaningful variation compared to control limits represented by the designated fidelity benchmark.

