### Study Power

Aim 2 analyses will compare study conditions based on family attendance and client outcomes over time, with client (N=60) as the unit of analysis. Assuming α=.05, a total sample size of N=60 (with 30 clients per condition), 3 measurement occasions with a moderate intercorrelation (*r*=0.50), and a moderate effect size of Cohen *d*=0.60, the analysis yields a power of 0.80. A smaller effect size of Cohen *d*=0.50 yielded a power of 0.65, assuming α=.05. These estimates are in line with the impacts seen in the studies on adolescents with ID but not SUD [60,62] and in the studies on adolescents with SU problems treated in usual care [79,94].

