Fam-AID contains 5 modules, each consisting of core treatment techniques that have a strong evidence base. In keeping with the principles of modular intervention design [36,160,161], clinicians are invited to select and implement any Fam-AID module, in any order, based on client needs, with a default of delivering them sequentially. The 5 Fam-AID modules are intended to galvanize and reinforce the family support system and equip the adolescent to cope with and ameliorate ID problems. Notably, module 4 draws its menu of core CBT techniques to treat ID-related problems (emotional acceptance, emotional exposure, and behavioral activation) from an existing evidence-based transdiagnostic protocol, which treats the underlying negative affect and emotional dysregulation [77] associated with adolescent IDs. In these ways, Fam-AID is distinct from other adolescent SUD+ID options due to how it combines a core elements strategy, family-focused interventions, and individual CBT techniques, which might enhance the often modest long-term impact of interventions for ID symptoms in usual care [162].

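### The one-way ANOVA across the five Fam-AID modules treats scores from the same clients and therapists as independent, so its error rate is not controlled, in a direction the protocol does not settle

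*Protocol article*

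**What the plan says.** In the protocol article, Plan of Analyses, the Aim 1 fidelity paragraph names the test for differences between modules: a "one-way analysis of variance to assess mean differences across modules in the Fam-AID condition to evaluate module preferences among therapists". It mentions no repeated-measures term, client effect or therapist effect.

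Other sections show where the module scores come from:

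- Fam-AID Fidelity Checklist: one instrument is used, "containing multiple items in each of the 5 Fam-AID modules", so each completed checklist scores all five modules.
- Study Procedures: clinicians are asked to complete a fidelity measure after every session with a study client, and "We project 4 therapists at each site (N=8) will participate".
- Plan of Analyses: coverage is counted per client across all modules, as the "proportion of clients who received at least 1 intervention from each of the 5 modules".
- Study Power: "a total sample size of N=60 (with 30 clients per condition", so 30 clients are in the Fam-AID condition.

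For Aim 2b, the same Plan of Analyses includes random effects for clients nested within therapists and for repeated measures within a person. The module comparison has neither.

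**The concern.** A one-way ANOVA compares independent groups. Here the five groups are five scores on the same clients, given by the same therapists. Two kinds of dependence are ignored, and they act differently on the F test.

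- **Within client.** If a client with high scores on one module tends to have high scores on the others, differences between clients enter the error term although they cancel out of the module contrasts. The test is then conservative. If more of one module means less of another, the effect reverses.
- **Within therapist.** If individual therapists favour particular modules, a few therapists' habits move the module means. The ANOVA counts clients as if each were separate evidence.

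The article leaves final module content to be settled during the study and presents the results as groundwork for a randomized trial. A non-significant result could hide a module that therapists avoid. A significant one could reflect the caseloads of two or three therapists.

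**Working it through.** The article gives no power, effect size or error rate for this test, so there is no stated figure to reproduce.

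**Inputs from the article:** n = 30 Fam-AID clients (Study Power), k = 5 modules (Fam-AID Fidelity Checklist), 8 therapists (Study Procedures). The level 0.05 is stated for Aim 2 and assumed here.

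**Assumed, because not stated:** one score per module per client; total variance 1; equal correlation ρ between any two module scores of a client, from -0.2 to 0.5; therapist-by-module variance share τ, either 0 or 0.20. The only correlation in the article ("3 measurement occasions with a moderate intercorrelation (*r*=0.50") is between time points of Aim 2 outcomes and does not inform ρ.

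**Step 1: client dependence only (τ = 0), no true module difference.**

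- Expected module mean square: 1 - ρ.
- The one-way error sum of squares is the client sum of squares, expectation (n-1)[1 + (k-1)ρ], plus the residual, expectation (n-1)(k-1)(1-ρ). Together: (n-1)k = 29 × 5 = 145. Divided by k(n-1) = 145 degrees of freedom, this is 1.
- The F ratio is therefore centred near 1 - ρ instead of 1. The 5% critical value of F(4,145) is 2.434, so the actual type I error is about P[F(4,145) > 2.434/(1-ρ)].

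For power, let one module lie 0.5 SD below the other four. The mean of the five falls by 0.1, the squared deviations sum to 4 × 0.1² + 0.4² = 0.20, and Cohen f = √(0.20/5) = 0.20. With client blocking, the noncentrality is 30 × 0.20/(1-ρ), for example 12 at ρ = 0.5, referred to F(4,116).

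| ρ | 2.434/(1-ρ) | Type I error, one-way | Power, one-way (simulated) | Power, client-blocked |
|---|---|---|---|---|
| -0.2 | 2.03 | 0.094 | 0.50 | 0.38 |
| 0 | 2.43 | 0.050 | 0.46 | 0.45 |
| 0.1 | 2.70 | 0.033 | 0.43 | 0.50 |
| 0.3 | 3.48 | 0.010 | 0.37 | 0.62 |
| 0.5 | 4.87 | 0.001 | 0.31 | 0.78 |

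Simulated type I errors agree: 0.094, 0.049, 0.033, 0.011 and 0.001. The client-blocked analysis stays at about 0.05 throughout. At ρ = -0.2 the one-way test rejects more often only because it is too liberal.

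**Step 2: add therapist-by-module variation (τ = 0.20).** Spread 30 clients over 8 therapists as six caseloads of 4 and two of 3. Then Σn²/30 = (6 × 16 + 2 × 9)/30 = 3.8.

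- Module mean square: (1 - ρ - τ) + 3.8τ.
- One-way error: (1 - τ) + τ × 26.2/29 = 0.80 + 0.181 = 0.981.
- Client-blocked error: (1 - ρ - τ) + 0.181.

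| ρ | Module MS | Ratio, one-way | Type I error, one-way (simulated) | Ratio, client-blocked | Type I error, client-blocked (simulated) |
|---|---|---|---|---|---|
| 0 | 1.56 | 1.59 | 0.195 | 1.59 | 0.194 |
| 0.3 | 1.26 | 1.28 | 0.120 | 1.85 | 0.269 |
| 0.5 | 1.06 | 1.08 | 0.073 | 2.20 | 0.360 |

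Blocking on client alone is no cure here. A therapist random intercept adds nothing either, because it cancels from every module contrast when each client is scored on all modules.

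**Step 3: a model with a therapist-by-module term.** This was approximated by testing module against therapist-by-module on therapist means, with (5-1)(8-1) = 28 error degrees of freedom. Simulated type I error under the Step 2 settings is 0.048 to 0.052. With τ = 0 and ρ = 0.5, power for the 0.5 SD scenario is about 0.71, against 0.78 with client blocking.

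**The case against.** A reader might infer that the planned test is simply far too insensitive, so that the study would report no disfavoured module when it cannot tell. The documents do not support that. It needs a clearly positive correlation between a client's module scores, and none is stated. The Discussion says that "clinicians are invited to select and implement any Fam-AID module, in any order, based on client needs", so more of one module may mean less of another. At a correlation of 0 the one-way test is about right, at 0.1 the loss is small (0.43 against 0.50), and at -0.2 or with therapist preferences it is too liberal. A positive correlation remains plausible: a client's five scores share therapist, rater and sessions, and the coverage benchmark asks for every module in every case. Plausible is not established, however.

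The article also does not state the unit or outcome of this ANOVA (client means, session scores or therapist means; therapist or observer checklist). The 150 scores behind the figures are an assumption. This qualifies the numbers, not the defect: with any of these units, the same people supply all five module scores. Reading one-way as shorthand for a repeated-measures ANOVA has no support in the text, and a version blocked on client alone would still leave out therapists.

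Finally, the test does not stand alone. The same paragraph plans descriptive frequencies of the most and least favoured modules and equivalence tests per module, and interviews add to these. That stands, and it limits the consequence.

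**Conclusion.** The point holds in this form: the named test does not fit the design, and its type I error is not controlled. It is a stated choice of method, not detail left to an analysis plan. Under the assumptions above, a nominal 0.05 lies anywhere from about 0.001 (correlation 0.5) to about 0.09 (correlation -0.2) from client dependence alone, and from 0.07 to 0.20 with a 20% therapist-by-module share and client correlations of 0.5 down to 0. The level is right only if both kinds of dependence are absent or happen to cancel. Neither a general loss of power nor a general excess of false positives can be claimed from the article. The correction is worth making because it is cheap and the result informs module revision. The weight is modest: this is a secondary Aim 1 analysis in a pilot.

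**What to change.** In Plan of Analyses, replace the one-way ANOVA with a linear mixed model of module score, with module as a fixed effect and random effects for client, therapist and therapist-by-module. Use small-sample degrees of freedom (for example Kenward-Roger) because there are only 8 therapists, and report the five module means with confidence intervals. State which score is modelled and from which checklist version. Keep the descriptive module frequencies.

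The cost is one or two sentences, with no new data and the mixed-model approach already planned for Aim 2. The statistical price is somewhat lower power than client blocking alone if therapists do not differ in module preference, about 0.71 against 0.78 at a correlation of 0.5. With 8 therapists the therapist-by-module variance will be estimated imprecisely, so the intervals should carry more weight than the F test.

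### The Aim 1 dose equivalence rule pools an SE with a benchmark that has no sample; with 8 therapists as the unit the interval cannot fit the ±10% margin at SD 0.50, and with 30 clients the rule has limited power

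*Protocol article*

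**What the plan says.** Plan of Analyses (Aim 1 fidelity benchmarks, dose) designates a benchmark, "which will be set (granting appropriate latitude for a pilot trial) for each module as mean 2.5 (SD 0.50"). For the margin, "an equivalence interval is defined as the benchmark +10% and –10" per cent. A 90% CI is then formed for the benchmark mean minus the study mean, using "the critical one-tailed value from the z distribution for the chosen value of α" and a pooled SE. The study mean is defined as "MT the average module score for study therapists". The decision rule is: "If the calculated CI falls within the equivalence interval, equivalence can be concluded". The test is run for each module on both the therapist and the observer version of the checklist.

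The section does not give the number of units behind the SE or a sample size for the benchmark. Study Power covers Aim 2 only.

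Three other places bear on the point. Study Procedures says "We project 4 therapists at each site (N=8) will participate". Specific Aims gives 30 Fam-AID cases. Study Measures scores each checklist item 0, 1 or 2.

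**The concern.** An equivalence rule of this kind can succeed only if the CI is narrower than the margin. If it is not, the result is fixed in advance by sample size and says nothing about how therapists delivered the modules. Two features of the written rule put this in doubt.

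- **The SE.** Pooling belongs to a comparison of two samples. Here one side is a value chosen by the investigators, so pooling adds sampling error that does not exist. The z limit errs in the other direction: it is too narrow for a mean based on about 8 independent units.
- **The unit.** The definition of the study mean points to the therapist, and only 8 are projected.

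Dose is one of the two fidelity benchmarks of Aim 1. The article says that promising pilot findings would set the stage for a randomized trial. An inconclusive equivalence test could be mistaken for evidence of poor delivery.

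**Working it through.** The plan states no power or CI width for this test, so there is no figure to reproduce.

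**Inputs.** Benchmark 2.5, SD 0.50, margin ±10%, 90% CI (Plan of Analyses); 8 therapists (Study Procedures); 30 Fam-AID clients (Specific Aims); items scored 0 to 2 (Study Measures).

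**Assumptions.** 0.50 is the SD of the scores being averaged. For the pooled SE, the benchmark is given the same n as the study, because none is stated. The interval is read as ±0.25 on the difference.

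**Step 1, margin.** 0.10 × 2.5 = 0.25, that is 2.25 to 2.75.

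**Step 2, half-width.** Half-width = 1.645 × SE. The one-sample SE is 0.50/√n; the pooled SE is 0.50 × √(2/n).

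**Step 3, chance of concluding equivalence at zero true difference.** P = max(0, 2Φ(0.25/SE − 1.645) − 1).

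| Unit | SE formula | SE | Half-width | Fits 0.25? | P on benchmark |
|---|---|---|---|---|---|
| 8 therapists | one-sample | 0.177 | 0.291 | no | 0% |
| 8 therapists | pooled | 0.250 | 0.411 | no | 0% |
| 30 clients | one-sample | 0.091 | 0.150 | yes | 73% |
| 30 clients | pooled | 0.129 | 0.212 | yes | 23% |

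The 23% lets the benchmark vary like a second sample. If it is held constant and only the formula pools, the room left is 0.250 − 0.212 = 0.038, and 2Φ(0.038/0.091) − 1 is about 32%. Either way, pooling more than halves the 73%.

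**Step 4, smallest n at which the CI fits at all.** (1.645 × 0.50/0.25)² = 10.8, so 11 (one-sample). Twice that is 21.6, so 22 per group (pooled).

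**Step 5, estimated SD at n = 8.** The one-sample CI fits if the observed SD is below 0.25 × √8/1.645 = 0.43. With a true SD of 0.50 this happens in about 36% of samples. Simulation gives about 7% for concluding equivalence on benchmark.

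**Step 6, t limits.** At n = 8 the one-sample half-width is 1.895 × 0.177 = 0.335.

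**Step 7, clustering of 30 clients in 8 therapists.** The design effect is 1 + (30/8 − 1) × ICC, with the ICC assumed. The one-sample SE is 0.50 × √(design effect/30), with z limits.

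| ICC | Design effect | SE | Half-width | P on benchmark |
|---|---|---|---|---|
| 0 | 1.000 | 0.091 | 0.150 | 73% |
| 0.1 | 1.275 | 0.103 | 0.170 | 56% |
| 0.3 | 1.825 | 0.123 | 0.203 | 30% |
| 0.5 | 2.375 | 0.141 | 0.231 | 11% |

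**Step 8, the scale.** The checklist maximum is 2, so 2.5 and the whole interval 2.25 to 2.75 lie above it. A perfect score of 2.0 is still 0.50 from the benchmark. If the benchmark were moved to, say, 1.0 (the midpoint of 0 to 2, used only as an example), the margin would be 0.10. The half-width with 30 clients is 0.150 under the more favourable SE, so the CI would no longer fit.

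**The case against.** The strongest reply is that the failure at n = 8 rests on choices the document does not make. It gives no unit. Fidelity is reported after every session, three sessions per client are coded, and benchmarks are monitored case by case, so clients or sessions could be the unit. The 0.50 is attached to the benchmark; therapist averages may vary less, and below 0.43 the one-sample CI fits. The pooled figure needs a benchmark n that is nowhere given. All of this stands, and it makes the n = 8 result conditional.

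A reader might infer that the rule also cannot succeed with 30 clients, or fails on most readings. The documents do not support that. At the stated benchmark the 30-client CI fits under both SE formulas, and the one-sample interval reaches 0.25 only near an ICC of 0.65. Ninety coded sessions also fit (0.087 or 0.123), though only if nesting is ignored. With clients as the unit the problem is low power, not impossibility. Outright failure at n = 30 before clustering needs a lower benchmark, which the dose test does not state.

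A reader might also infer that every module and both reporters will fail because of imprecision and be declared unfaithful. That goes too far. Taken literally, the rule fails because the interval is off the scale, whatever the n. No go/no-go decision is tied to this test, and coverage, module comparisons and control charts are also planned.

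The reply does not rescue the pooled SE. The benchmark is designated; giving it an SD does not give it a sample.

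**Conclusion.** The point holds in a limited form. The SE and the z limits are wrong as written, because a fixed benchmark contributes no sampling error and the independent units are few. With the therapist as unit, which the definition of the study mean suggests, and SD 0.50, the half-width of 0.29 to 0.41 exceeds the 0.25 margin, and equivalence is out of reach even exactly on benchmark (about 7% if the SD is estimated, one-sample). With 30 clients the rule can work at 2.5, with a 73% (one-sample) or 23% (pooled) chance before clustering.

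These figures rest on 0.50 being the SD of the averaged scores and, for the pooled results, on an equal benchmark n. They also take 2.5 at face value, although the checklist cannot produce it. Correcting the 2.5 alone would not settle the matter, because the percentage margin shrinks with the benchmark.

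**What to change.** 1. Treat the benchmark as a fixed constant. Replace the pooled SE with the one-sample SE of the study mean, from client-level module means with a therapist random effect, and use t limits. State the unit and n.
2. When reconciling the benchmark with the 0 to 2 scale, state the margin in absolute scale points and justify it by how much deviation in fidelity is acceptable. It should not be worked backward from the sample size. As a guide to what 30 clients can resolve at SD 0.50, 80% on benchmark needs (1.645 + 1.282) × 0.0913 = 0.27 points before clustering, and more after it.
3. Report each module mean with its 90% CI against the benchmark, for both reporters, and say that a CI crossing the margin is inconclusive and not evidence of failed fidelity.

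The cost is wording in the analysis plan; no new data are needed. The t limits and the therapist effect widen the interval, so step 1 alone does not make the test pass with 8 therapists (half-width 0.335 at n = 8). The downside is that the dose result may be descriptive rather than pass/fail.

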### Specific Aims of the Study

In year 1, this study will develop a Fam-AID implementation toolkit during a three-part *pilot stage* at 1 pilot site by (1) soliciting provider input on Fam-AID components; (2) creating video-based training and fidelity procedures, leveraging the research team’s existing training and consultation resources in both core family-based interventions [75,76] and adolescent-focused transdiagnostic techniques [77] for adolescent behavior problems; and (3) piloting the toolkit with 4 to 6 clients. In years 2 to 3, this study will conduct an *interrupted time series* evaluation for 60 adolescent SUD+ID cases across 2 sites serving diverse clients: 30 cases will receive treatment as usual (TAU), and then following clinician training, 30 new cases will receive TAU enhanced by Fam-AID.

This protocol development study has 2 specific aims:

Aim 1 (protocol feasibility): in the Fam-AID condition only, the study will evaluate (1) protocol acceptability via client and therapist qualitative interviews and (2) fidelity benchmarks via therapist- and observer-report fidelity measures of protocol coverage (Is each module delivered in at least 1 session?) and protocol dose (Is the average module extensiveness score greater than the mean of the fidelity measure?).Aim 2 (protocol outcomes): in comparing the TAU only condition versus the TAU+Fam-AID condition, the study will examine the protocol’s impacts on (1) family member session attendance using clinic logs and (2) adolescent ID-related symptoms (emotion regulation, depression, and anxiety), SU, and family communication about SUD+ID at 3-month and 6-month follow-up. Overall, these pilot-scale protocol viability and impact findings, if promising, will set the stage for a randomized trial to examine the effects of Fam-AID on immediate and ultimate outcomes in a larger community sample.

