### Fam-AID Training and Fidelity Monitoring

Site clinicians will be trained for 6 hours. The session will feature video-based training [117,118] in Fam-AID modules and techniques. Thereafter, consultation at each site will include bimonthly live consultation with a protocol expert focused on equipoise between protocol fidelity and case tailoring, along with continuous feedback from therapist- and observer-report fidelity data, which is emailed directly to clinicians and used in live consultation to enable rapid adjustment in protocol delivery [119-121]. Two main fidelity benchmarks will be monitored for each case. These benchmarks include clinicians delivering interventions for every module in at least 1 treatment session (ie, coverage) and clinicians performing at or above the mean scale score for intervention extensiveness on the Fam-AID Fidelity Checklist (described in the Study Measures section) for at least 1 technique from each module (ie, dose), with both therapist- and observer-report checklist versions being tracked.

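### The planned equivalence test of fidelity dose uses a benchmark of 2.5 on a checklist whose average cannot exceed 2, so its sections must be reconciled and the rule made one-sided

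*Protocol article*

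**What the plan says.** All references are to the protocol article.

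- **Fam-AID Fidelity Checklist.** The parent instrument rates each technique on a "3-point Likert-type scale: 0 (not at all), 1 (a little bit or moderately), or 2 (quite a bit or extensively" scale. The trial's version keeps that form: "The Fam-AID Fidelity Checklist mimics the ITT structure, containing multiple items in each of the 5 Fam-AID modules". The observer version "is an identical measure with instructions for observer coding".
- **Plan of Analyses, Aim 1 fidelity benchmarks.** Average extensiveness scores, therapist-reported and observer-reported, are tested for equivalence to a benchmark "which will be set (granting appropriate latitude for a pilot trial) for each module as mean 2.5 (SD 0.50". The equivalence interval is the benchmark plus and minus 10%. A 90% confidence interval is built for M_R − M_T, the benchmark minus the average module score, and equivalence is concluded if it falls inside the equivalence interval. Therapists are then plotted on a control chart against "control limits represented by the designated fidelity benchmark".
- **Specific Aims of the Study.** Dose is put as a question: "Is the average module extensiveness score greater than the mean of the fidelity measure".
- **Fam-AID Training and Fidelity Monitoring.** Dose is monitored for each case as "clinicians performing at or above the mean scale score for intervention extensiveness on the Fam-AID Fidelity Checklist", for one or more techniques in each module.

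**The concern.** The benchmark and the scale cannot both be right if module scores are averages of items. The only inferential test planned for dose would then return the same answer however well therapists deliver the modules, and so would carry no information about fidelity.

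Dose is one of two main fidelity benchmarks, and fidelity is half of Aim 1 (feasibility). The Specific Aims say that promising findings would set the stage for a randomized trial. If the fault surfaces only after scores are in, any replacement benchmark will have been chosen with the data in view.

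**Working it through.** **Inputs.** Item range 0 to 2 (Fam-AID Fidelity Checklist). Benchmark M_R = 2.5, SD 0.50, limits ±10%, 90% interval with one-tailed z = 1.645 (Plan of Analyses). The article gives no sample size for this test. The values of n below, and a one-sample standard error SD/√n, are my assumptions.

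**1. The plan's equivalence interval.** 2.5 × 0.9 = 2.25 and 2.5 × 1.1 = 2.75. As a margin on the difference, 2.5 × 0.10 = 0.25.

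**2. The ceiling.** An average of items that each score at most 2 is at most 2.00. The benchmark is 2.5 − 2.0 = 0.50 above it, or one stated SD. The lower equivalence limit is 2.25 − 2.00 = 0.25 above it. Any benchmark above 2/0.9 = 2.22 has a ±10% interval lying wholly off the scale.

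**3. Standard reading: the interval for M_R − M_T must lie within ±0.25.** Take the best possible result, M_T = 2, so that M_R − M_T = 0.50. The interval is 0.50 ± 1.645 × SD/√n.

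| n | SD | 90% CI of M_R − M_T | Within ±0.25? |
|---|---|---|---|
| any | 0 | 0.50 to 0.50 | No |
| 8 | 0.50 | 0.21 to 0.79 | No |
| 30 | 0.50 | 0.35 to 0.65 | No |
| 90 | 0.50 | 0.41 to 0.59 | No |
| 1000 | 0.50 | 0.47 to 0.53 | No |

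The result does not depend on n or SD. The interval is centred on M_R − M_T, which is never below 0.50, so its upper limit is never below 0.50 and always exceeds 0.25.

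**4. Literal reading: the interval for M_R − M_T must lie within 2.25 to 2.75.** The text compares an interval for a difference with limits placed around the benchmark itself. The lower limit then requires 2.5 − M_T − 1.645 × SD/√n ≥ 2.25, that is M_T ≤ 0.25 − 1.645 × SD/√n. With SD 0.50:

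- n = 30: M_T ≤ 0.25 − 0.15 = 0.10
- n = 90: M_T ≤ 0.25 − 0.09 = 0.16

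The upper limit is met by any M_T of 0 or more at these sizes. On this reading, only near-absent delivery passes.

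**5. The three statements of dose.**

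| Section | Criterion | Attainable on 0 to 2? |
|---|---|---|
| Specific Aims | Module average above the mean of the measure | Yes, if that mean is the scale midpoint, (0 + 2)/2 = 1.0 |
| Training and Fidelity Monitoring | At or above the scale mean for at least one technique per module | Yes, on the same assumption |
| Plan of Analyses | Equivalent to 2.5 ± 10% | No (step 3) |

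The first two are one-sided and the third is two-sided, so they differ in direction as well as in value.

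**6. Would moving the benchmark be enough?** As an illustration, put it at 1.0 and keep the two-sided ±10% rule. The interval becomes 0.90 to 1.10. A group averaging 1.5 has M_R − M_T = −0.50, and one averaging 2.0 has −1.00. Both fall outside ±0.10 and fail for delivering more than the benchmark. At n = 30 and SD 0.50 the half-width of 0.15 exceeds the margin of 0.10, so even an average of exactly 1.0 could not pass.

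**The case against.** **Module scores might be totals.** With two items scored 0 to 2 the maximum is 4, and 2.5 is reachable. The article never says outright that items are averaged within a module, and the average could be taken over therapists. That leaves some doubt, but it is the weaker reading: the Specific Aims and the Plan of Analyses both speak of averages, and a single 2.5 for every module suits item means better than totals over item sets that may differ in length.

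**The adapted checklist might use another response format.** A value of 2.5 is the midpoint of a 1-to-4 or a 0-to-5 scale, so it may have been carried over. Neither scale is described. This would explain the conflict without removing it.

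**The pilot stage may settle it.** Pilot phase 3 is meant to help optimize delivery benchmarks, so there is a natural moment to correct the figure. The published figures are still incompatible.

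**Stronger readings that the article does not support.** A reader might infer that Aim 1 dose must fail altogether. It need not, because the criteria in the Specific Aims and in Training and Fidelity Monitoring can be met on a 0-to-2 scale. Nor is failure certain on every reading of the equivalence rule, as step 4 shows. A reader might also infer that every therapist will breach the control limits. All would plot below 2.5, but the limit widths are not given; if they were set 2 or 3 SDs below (my assumption), they would be 1.5 or 1.0, both attainable. No site-level dose test is planned. Finally, no go/no-go rule rests on dose alone, since acceptability and coverage also belong to Aim 1.

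**Conclusion.** The point holds for the equivalence test and for the benchmark behind the control chart. Perfect delivery sits 0.50 from the benchmark, twice the 0.25 margin. On the standard reading, no module can pass under either reporter at any sample size; on the literal reading, the rule rewards near-zero delivery. The Plan of Analyses also disagrees, in value and in direction, with the two other statements of dose.

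This rests on two readings of the article: that the Fam-AID checklist keeps the 0-to-2 items of its parent instrument, and that a module score is an average of items. Calling the other two criteria attainable assumes that the mean they refer to is the scale midpoint. The conclusion under the standard reading needs no assumption about n or SD; the cut-offs of 0.10 and 0.16 under the literal reading do. It should be corrected before data collection, which the article says begins in April 2025.

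**What to change.** 1. Reconcile Specific Aims, Training and Fidelity Monitoring, Fam-AID Fidelity Checklist and Plan of Analyses so that all use one dose benchmark inside the checklist's actual scoring range. If 2.5 belongs to a different response format, correct the stated scale instead. State that a module score is the average of its items.
2. Replace the two-sided equivalence rule with a one-sided, at-or-above (non-inferiority) test. Conclude that the benchmark is met if the upper confidence limit of M_R − M_T lies below a stated margin on the difference scale. Delivery above the benchmark then cannot fail.
3. Give that margin in points. A margin of 10% of the benchmark shrinks as the benchmark falls, and step 6 shows that it can become narrower than the interval's half-width.
4. Base the control chart on the corrected benchmark.

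In choosing the value, note that any technique delivered at all scores at least 1. A threshold of 1.0 applied to one technique per module in one session would therefore repeat the coverage benchmark.

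The cost is a wording change to the protocol and analysis plan, provided the response format stays as described. Changing the format would also mean revising both versions of the checklist before use.
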